#### Economic analysis

Mean, median, and interquartile (semi-IQ) will be used to describe the costs for the two groups. Cost-effectiveness analysis will be performed on the main outcome: reduction in number of leakages (%) one year after randomization and expressed as a ratio of incremental costs and percentage of leakages. In order to verify the robustness of the economic analysis, a sensitivity analysis will be conducted on the hypothesis that the costs for each participant should be between the 25th and 75th percentiles of the cost distribution.

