##### Sample size calculation

Sample size was calculated so as to ensure the adequate power and type I error rate for testing the primary hypothesis of non-inferiority of the group-based intervention relative to the individualized intervention, in achieving the relative reduction (in %) in the number of UI episodes at one year. Sample size calculations followed CONSORT Guidelines for non-Inferiority trials [68]. First, based on clinical relevance [69] (minimum clinically relevant difference = 10%) and our pilot data [18–22], we set the “margin of equivalence” (i.e. the upper limit of the non-inferiority interval) as corresponding to a 10% difference between mean % reduction in the number of UI episodes in the “standard treatment” of the individualized intervention minus the group-based intervention arm. This implies that we test the null hypothesis H0:d ≤ 10%, where d denotes the true difference between the mean relative reductions in the number of UI episode in the two arms (individualized minus group-based) against the alternative hypothesis H1:d > 10%. According to the CONSORT guidelines, this choice of the “margin of equivalence” implies that the non-inferiority hypothesis should be rejected whenever the upper bound of the two-tailed (1 – 2α)% confidence interval (CI) for the difference between the two mean % reductions exceeds 10%. In the specific context of a non-inferiority trial, α is the selected risk of a false acceptance of the non-inferiority hypothesis (based on a one-tailed CI-based test, equivalent to an independent-group t-test); i.e. of a false conclusion that a truly inferior intervention is equally efficacious as the “standard treatment” [68].

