To err on the conservative side, we relied on the “standard” 95% CI, which corresponds to a stringent one-tailed type I error rate of α = 0.025 (2α = 1–0.95 = 0.05). Similar to other recent non-Inferiority trials (e.g. [70, 71]) and CONSORT guidelines [68], for the purpose of sample size calculation, we assume that the true difference between the mean reductions (%) achieved by the two interventions will be zero (i.e. that they are equally effective). Note that this assumption of equivalence of the two interventions being compared in our trial is consistent with both (a) clinical expectations and (b) (limited) published evidence concerning young and middle-aged UI women [72–74]. Finally, both published trials, which evaluated similar interventions in older women, reported within-group standard deviations (SD) of the individual % reduction scores of about 27% [44, 75]. Accordingly, we assumed SD = 27% in our calculations.

Under the above assumptions, we estimated the sample size needed to ensure high (90%) power to demonstrate the non-inferiority of the group-based intervention (assuming, as mentioned above, that the true difference is 0%). Thus, we calculated N, for which the probability that the upper boundary of the two-tailed 95% CI for the difference in the mean relative reduction (Individual – Group) excludes the “upper threshold of non-inferiority” (10% difference), will reach at least 90%. The sample size calculations were performed using the program in the PASS software package, designed specifically for power/sample size estimation for non-inferiority trials [76]. Under the assumptions outlined above, we will need 155 participants per group, for a total of 310 individuals. We also need to account for possible losses to follow-up, as we expect a 15% attrition rate by the end of the one year, based on both our pilot data and similar published trials [16, 17, 22, 51]. Thus, we will recruit an additional 54 participants per group, increasing the total number of participants to 364 (364*(1–0.15) = 310).

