## Discussion

Considering demographic projections, human resources, and health system constraints, there is a pressing need to scale up evidence on the long-term benefits of low-cost interventions in urinary incontinent aging women and thereby improve clinical, functional, and social outcomes of this highly prevalent condition in this subpopulation. This GROUP trial, the first adequately powered RCT, seeks to study the non-inferiority of group PFMT in comparison to individual one-on-one PFMT in aging women with UI. If group-based PFMT classes prove to be equally effective, as well as more cost-effective, compared to individual one-on-one PFMT sessions, this trial could have a positive impact on the accessibility of continence care for aging women in Canada.

The results of this RCT will be relevant to clinicians and clinical decision-makers as well as to administrative stakeholders. It will have implications for the organization and the administration of continence care services. Ultimately, the results may influence the cost of treatment per individual, the accessibility of conservative management, and the use of more invasive UI interventions such as medication and surgery in older UI women.

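### The cost-effectiveness ratio is a poor summary when the effect difference is near zero, which is the scenario the trial plans on

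*Protocol article*

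**What the plan says.** All references are to the Protocol article.

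- **Economic analysis.** "Cost-effectiveness analysis will be performed on the main outcome: reduction in number of leakages (%) one year after randomization", with the result "expressed as a ratio of incremental costs and percentage of leakages". Costs are also described by arm (mean, median, interquartile range). The one robustness check limits costs to the range between the 25th and 75th percentiles.
- **Sample size calculation.** For planning, "we assume that the true difference between the mean reductions (%) achieved by the two interventions will be zero". The authors add that "this assumption of equivalence of the two interventions being compared in our trial is consistent with both (a) clinical expectations" and limited published evidence. The margin is a "10% difference between mean % reduction in the number of UI episodes", taken as individual minus group.
- **Rationale for a non-inferiority trial.** Lower cost of the group format is one of the listed reasons for the design.
- **Discussion** (and, in similar terms, the Abstract and Background). The practical conclusion has two parts: "If group-based PFMT classes prove to be equally effective, as well as more cost-effective".

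**The concern.** An incremental ratio divides the cost difference by the effect difference. Here the plan expects the numerator to be clearly different from zero and the denominator to be centred on zero. Three things follow.

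- The sign of the ratio depends on which side of zero the effect estimate happens to fall.
- Its size grows without limit as the estimate approaches zero.
- Its meaning changes with the sign. Taken as group minus individual, with group cheaper, a positive ratio means cheaper and worse, not the usual cost per unit gained. A negative ratio means cheaper and better, and there a larger benefit gives a smaller absolute ratio.

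What is at stake is the second half of the trial's message, that group training is more cost-effective. The stated summary for it is hardest to interpret when the first half, equal effectiveness, is true. The percentile check on costs leaves the denominator untouched.

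**Working it through.** **Inputs.** SD of the individual percentage reduction: "Accordingly, we assumed SD = 27% in our calculations". Type I error: "which corresponds to a stringent one-tailed type I error rate of α = 0.025". Power 90%, margin 10 points, true difference 0, 155 evaluable women per arm (all Sample size calculation). Twelve weekly one-hour sessions (Interventions; PFMT sessions). Group hours divided by eight (Costs related to interventions). Up to three optional 20-minute private sessions in the group arm (Group-based PFMT).

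**1. The plan's own figure.** Normal approximation: n = 2 × 27² × (1.960 + 1.282)² / 10² = 153.2, so 154 per arm. With the noncentral t distribution, 155 per arm gives power 0.9015. The stated 155 is reproduced, so these inputs are the ones the plan uses.

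**2. Precision of the denominator.** SE = 27 × √(2/155) = 3.07 points. The 95% CI half-width is 1.96 × 3.07 = 6.01 points.

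**3. Behaviour at a true difference of 0.**
- Probability that the estimate falls on either given side of zero: 0.50.
- Probability that it lies within 1 point of zero: 2Φ(1/3.07) − 1 = 0.26.
- Non-inferiority is accepted if the estimate (individual minus group) is below 10 − 6.01 = 3.99. Among trials that pass, individual treatment still looks better in (Φ(3.99/3.07) − 0.5) / Φ(3.99/3.07) = 0.45.

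**4. Interval for the ratio.** The Fieller confidence set for a ratio is unbounded whenever the CI of the denominator includes zero. The probability of that is Φ(1.96 − d/3.07) − Φ(−1.96 − d/3.07), where d is the true difference, individual minus group:

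| True difference (points) | Individual looks better | Effect CI includes 0 |
|---|---|---|
| 0 | 0.50 | 0.95 |
| 3 | 0.84 | 0.84 |
| 5 | 0.95 | 0.63 |
| 8 | 0.995 | 0.26 |

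**5. Size of the ratio, as an illustration.** Count programme time only and hold it fixed. Individual treatment takes 12 therapist-hours per woman and group treatment 12/8 = 1.5, a saving of 10.5 hours. At a true difference of 0, the absolute ratio 10.5/|estimate| has quartiles of 3.0 and 10.8 hours per point and a central 95% range of 1.5 to 109. If all three optional sessions are used, the saving is 12 − 2.5 = 9.5 hours and these figures shrink by about a tenth. Pad and consultation costs, and the sampling variation of costs, cannot be sized from the document.

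**6. Two nearly identical trials.** Let the group arm be 0.5 points better in one and 0.5 points worse in the other. The ratios (group minus individual) are −10.5/0.5 = −21 and −10.5/−0.5 = +21 hours per point. Incremental net benefit is (value per point × effect difference) − cost difference. With an arbitrary value of 1 hour per point, it is 0.5 + 10.5 = 11.0 and −0.5 + 10.5 = 10.0. It barely moves, as it should.

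**The case against.** The strongest reply is that the ratio will not stand alone. The Economic analysis section describes costs by arm, the Objectives promise a comparison of direct costs, and the Data analysis section gives the effect difference with a 95% CI against the 10-point margin. A reader might infer that the economic conclusion will be read off the ratio alone. The documents do not support that. Both components will be visible, no threshold or decision rule is attached to the ratio, and effectiveness is judged first by the non-inferiority test. This stands, and it limits the point to the choice of summary.

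Second, zero is a planning assumption, and the Background and rationale also raise possible longer-term benefit of the group format. The even split of signs holds only at zero; at 3 points it is already 84 to 16. This also stands. However, the authors call zero clinically expected, and the unbounded interval remains common for true differences well inside the margin.

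Third, it is tempting to argue that if group training were truly 3 points worse, 16% of trials would still show it as cheaper and better. That is ordinary sampling error in the effect estimate, which any summary would carry, so it is no argument against the ratio.

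Fourth, the wording is loose: incremental attaches grammatically to costs. A between-arm difference is the natural reading of the denominator, but it remains a reading.

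Last, a condensed article may leave bootstrap methods, planes and acceptability curves to a fuller document. Their absence is not the complaint. The complaint concerns the summary that this text does fix.

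**Conclusion.** The point holds in a limited form. The stated cost-effectiveness summary behaves badly in the scenario the trial plans on. At a true difference of 0 its sign is left to chance and its confidence set is unbounded in about 95% of trials; at 3 points the set is still unbounded in about 84%. The stated robustness check does not address this.

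This rests on an SD of 27, 155 evaluable women per arm, normal sampling of the effect difference, a cost difference whose sign is settled in favour of the group format, and a denominator read as the between-arm difference. Unbounded describes the interval; a realised ratio is finite unless the estimated difference is exactly zero.

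It would go too far to say that the trial cannot distinguish a cheap and equal group format from a cheap and slightly worse one. That is true of the bare ratio but not of the planned results taken together. The primary non-inferiority inference is unaffected. The change should be made, but it concerns a secondary economic summary.

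**What to change.** In the Economic analysis section:

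- Make the cost-effectiveness summary the incremental net benefit, over a pre-stated range of values per percentage point of leakage reduction.
- Accompany it with the joint bootstrap distribution of the cost and effect differences, shown as a cost-effectiveness plane and an acceptability curve.
- Report the difference in mean cost with a bootstrap 95% CI next to the effect difference. The cost difference should not replace the joint summary, since alone it ignores effect.
- State that the denominator of any ratio is the between-arm difference, and give a ratio only with its quadrant and joint uncertainty. Do not make its reporting conditional on a significant effect difference: under the planning scenario that rule would suppress it in about 95% of trials.

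No new data are needed. The cost is revised wording, some bootstrap programming, and the need to choose the range of values per point in advance, for which the document offers no anchor.

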**Discussion:**

Should this study find that a group-based approach is not less effective than individual PFMT, and more cost-effective, this trial will impact positively continence-care accessibility and warrant a change in clinical practice.

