#### Individualized PFMT

The only specificity of this treatment group is that women participate in one-on-one, 1-h sessions with intra-vaginal electomyography (EMG) biofeedback under the supervision of an experienced physiotherapist. This treatment approach is in line with clinical practice in Canada [53].

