#### Group-based PFMT

The only specificity for this treatment group is that women participate in groups of eight in a weekly 1-h session, under the supervision of an experienced physiotherapist. They are also offered up to three optional private (20 min) sessions with the physiotherapist leading their group (either before or after a group session) to ensure understanding and correct performance of a PFM contraction – as confirmed by vaginal digital palpation [17]. This treatment approach is consistent with Bo’s PFM exercise class [54] and our more recent pilot cohort studies indicating it is both feasible and effective intervention for UI in aging women [18, 55]. In case of slow recruitment, we have established a minimum group size of six participants in order to avoid delays for those assigned to group physiotherapy.

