##### Costs related to interventions

The DBICI, a universally applicable questionnaire, has been adapted to measure the intervention costs for the two treatment groups [41, 65]. The validated DBICI has been used in RCTs with community-dwelling populations of women aged 40 years and over for non-surgical UI interventions [66] and is recommended by the International Consultation on Incontinence Research Guidelines [10, 42]. Section 1 of the DBICI documents, monthly self-reported personal incontinence expenditures (disposable and re-usable incontinence products), is used integrally. Section 2 deals with treatment expenditures and has been adapted as follows: (1) Treatment costs: rather than self-reported, treatment duration (in h) for each participant is based on statistics maintained by the research coordinators using a standardized form developed for a previous cost-effectiveness study [67]. The number of hours is multiplied by the mean hourly salary of the physiotherapists participating in the study. For the group-based PFMT, the total number of hours will be divided by the number (n = 8) of intended class participants (i.e. not actual attendance); (2) Other consultations: the frequency of visits to incontinence-related medical professionals is documented by category (general practitioners and specialists). A research assistant will phone participants at three months and six months post intervention in order to collect information. Estimated costs are based on the frequency and a mean cost per visit based on the public health system regulations for each category (Régie de l’assurance maladie du Québec). UI medication costs is excluded from the trial as those with UI medication are excluded at study entrance.

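### The one economic robustness check stated confines costs to the interquartile range: it is undefined, blind to a costly minority if costs are trimmed or capped, and on no reading measures uncertainty in the mean cost difference

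*Protocol article*

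**What the plan says.** The Economic analysis section of the protocol article has three elements.

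- Description: "Mean, median, and interquartile (semi-IQ) will be used to describe the costs for the two groups".
- Main result: a cost-effectiveness measure on the one-year percentage reduction in leakages, "expressed as a ratio of incremental costs and percentage of leakages". No percentile restriction is attached to it.
- Robustness: "In order to verify the robustness of the economic analysis, a sensitivity analysis will be conducted". Its premise, as worded there, is this: "costs for each participant should be between the 25th and 75th percentiles of the cost distribution". No other economic robustness check is named.

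Costs related to interventions lists what is counted: incontinence products, physiotherapist hours multiplied by a mean hourly salary, and visits to general practitioners and specialists. UI medication is not costed. For group treatment, "the total number of hours will be divided by the number (n = 8) of intended class participants". In the individual arm "women participate in one-on-one, 1-h sessions" weekly for 12 weeks. Of women in the group arm the protocol says: "They are also offered up to three optional private (20 min) sessions".

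The abstract's Discussion makes a change in practice depend on group treatment being "not less effective than individual PFMT, and more cost-effective".

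**The concern.** An incremental cost ratio depends on the mean cost per arm, and costs of this kind are usually right-skewed, so a few expensive women can carry much of the mean. Most of the treatment-hours component is fixed by the design and favours the group arm. The components that could offset that saving, products and consultations, can differ greatly between women and would show in the upper tail. A check confined to the middle of the distribution largely preserves the built-in saving and removes or flattens the part that could overturn it. Agreement between the check and the main result would then say little about whether the saving survives high-cost women, yet the plan would present it as robustness. Cost-effectiveness is one of the two conditions for the practice-changing conclusion, so the check should be able to test it.

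**Working it through.** **Figures from the protocol.** The economic section states no numerical result to reproduce. The sample size of 155 per arm, used below, does reproduce: with margin 10, SD 27, true difference 0 and one-sided alpha 0.025, power is 0.8997 at 154 and 0.9015 at 155.

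**Built-in difference in hours.** Individual: 12 × 1 h = 12 h. Group: 12 h / 8 = 1.5 h, plus 0 to 3 × 20 min = 0 to 1 h if private sessions are charged in full (assumed). The gap at full attendance is 12 − 2.5 = 9.5 h to 12 − 1.5 = 10.5 h. At assumed salaries of $30, $40 and $60 per hour this is $285–315, $380–420 and $570–630 per woman.

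**What trimming keeps.** The 25th–75th percentile range holds about half the women: 155 of 310 evaluable, or 182 of 364 randomised.

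**Illustration (all prices assumed).** 155 women per arm; $40 per hour; 93% attendance in the individual arm; 0 to 3 private sessions, averaging 0.5 h; other costs exponential with mean $150; a high-cost event averaging $5,000 in 5% of the individual arm and in a varying share of the group arm (no events in either arm in the 0% row). Without events, the expected difference, group minus individual, is 40 × (1.5 + 0.5) − 40 × 12 × 0.93 = 80 − 446 = −$366; the simulation gives −$367. Entries are mean differences in dollars; negative means group is cheaper. The adverse corner puts the group arm at its 75th percentile and the individual arm at its 25th.

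| Group events | All women | Trim within arm | Trim pooled | Cap within arm | Cap pooled | Adverse corner |
|---|---|---|---|---|---|---|
| 0% | −367 | −370 | −192 | −370 | −274 | −207 |
| 15% | +131 | −342 | −181 | −331 | −230 | −91 |
| 20% | +380 | −315 | −173 | −269 | −207 | +96 |
| 24% | +586 | −265 | −164 | −94 | −184 | +692 |
| 30% | +884 | −66 | −146 | +375 | −141 | +2,155 |
| 40% | +1,375 | +518 | −67 | +1,016 | +16 | +3,537 |
| 50% | +1,875 | +1,250 | +562 | +1,575 | +640 | +4,288 |

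At 20%, both trims show a group saving in 100% of replicates. The within-arm trim shows a saving in 68% at 30%, 2% at 40% and 0% at 50%; the pooled trim in 89% at 40% and 13% at 50%. At 20% the pooled trim keeps on average 43 group and 111 individual women, so the retained sets are no longer comparable by randomisation.

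**When there is a reversal to hide.** The all-women mean turns against group when C × (p_group − p_ind) exceeds the built-in saving, where C is the extra cost of an event. With a saving of $367, p_ind = 5% and p_group at 25%, C must exceed 367 / 0.20 = $1,835, or 1,835 / 40 = about 46 physiotherapist hours. At C = $2,000 the turn comes at 5% + 367 / 2,000 = 23.4%; the simulated means agree (−$67 at 20%, +$135 at 30%).

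**Sensitivity to background cost.** With other costs averaging $600 and 20% events, the all-women difference is +$379. The within-arm trim gives −$164 (saving in 93% of replicates) and the pooled trim +$5 (46%).

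**Quartiles are not uncertainty.** In the 0% row, moving each arm between its quartiles spans −$534 to −$207, a width of $327. The variances are about 1,600 × 12 × 0.93 × 0.07 + 150² = 23,750 (individual) and 1,600 × 0.139 + 150² = 22,722 (group). The standard error of the mean difference is √((23,750 + 22,722) / 155) = 17.3, so the 95% interval is about −367 ± 34, a width of $68. The quartile span does not shrink as the sample grows; the interval does.

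**The case against.** Four points are made on the other side, and much of them stands.

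**The check can fail.** A reader might infer that it confirms a group saving whatever the data show. It does not. An extra cost averaging $500 across the whole group arm gives +$136 on all women and +$106 after within-arm trimming, with a saving shown in 0.2% of replicates. Events in 40% of the group arm also reverse the within-arm trim.

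**Nobody need be discarded.** A reader might infer that half the women are always dropped. That is one reading. Capping or varying costs over the quartiles keeps everyone, and the adverse corner is demanding: +$96 at 20% events, with a saving shown in only 53% of replicates.

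**The tail may be too small to matter.** Only products, physiotherapist hours and consultations are costed. In hour units (individual mean 11 h, group mean 2 h, gap 9 h), an event worth 20 h gives break-even only at 5% + 9 / 20 = 50% of the group arm, and there the trims show a saving less often (27% within arm, 23% pooled) than the full data (50%). Nor do the documents support reading every high-cost woman as a treatment failure, since product use can also reflect baseline severity.

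**The check is supplementary.** The main ratio has no restriction and mean costs are reported, so a tail-driven result would show as a discrepancy. The absence of a bootstrap from a condensed article is not in itself a fault.

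What remains is a fault in the method that is stated. The possible readings give opposite answers on the same data. Trimming and capping cannot test whether a saving survives a costly minority. Where the analyses diverge, nothing says whether the tail is noise to be set aside or a real cost.

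**Conclusion.** The point holds in a limited form. The stated check is ambiguous in two respects: drop, cap or vary; per arm or pooled. Under trimming or capping it is insensitive to a high-cost minority below about a quarter of an arm, or up to about 40% with pooled trimming, and can then show a saving when the mean over all women shows a loss. In the illustration with 20% events in the group arm, the gap between the two answers is 380 + 315 = $695 within arm and 380 + 173 = $553 pooled. Trimming additionally conditions on a post-randomisation variable. No reading quantifies uncertainty in the mean cost difference.

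The size depends on salary, background cost and event cost, none of which the protocol gives. A hidden reversal below the quarter mark needs an event cost above about $1,835 under the $40 per hour assumptions; with cheaper events the base case would not reverse there. The main economic result keeps every woman and is not impugned. This should be corrected, but it concerns a supporting analysis of a secondary question.

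**What to change.** In the Economic analysis section, replace the robustness sentence with an analysis that keeps all participants:

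- a bootstrap 95% confidence interval for the difference in mean cost, resampling within arm and centre;
- one-way sensitivity analyses varying the hourly salary and the cost per visit over ranges fixed before the unblinded data are seen.

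If the quartile analysis is kept, state whether costs are dropped, capped or varied and whether percentiles are per arm or pooled. Label it only as a check for outlier influence, not as evidence that the saving is robust, and report it beside the all-participant result.

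The cost is a change of wording and a few lines of code on data already being collected. The price is a little more analysis and a reported interval that may be wide if costs are skewed.
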